### Specific aims:

1. To determine the incidence of NVAF diagnosis in England from the year 2009 to 2019.
2. To determine the proportions of patients with NVAF and those with NVAF and cancer who were prescribed OACs, antiplatelet alone or no treatment.
3. To examine the temporal trends of prescribing different types of OACs (i.e. VKAs and NOACs), and assess the factors associated with not prescribing OACs including patient demographics, socioeconomic status, history of cancer and other comorbidities, stroke and bleeding risk.
4. To assess the effect of OACs prescribing vs. no OACs on the clinical outcomes (stroke, bleeding, and death) in a comparative cohort of NVAF patients eligible for anticoagulation after controlling for patients' comorbid conditions, frailty, age, and antiplatelets use.
5. To assess the rate of clinical outcomes (i.e. bleeding recurrence, stroke, and mortality) after MB events and how they relate to OACs resumption and the timing of restarting OACs after the MB event.
6. To explore the variability across patient groups regarding OACs resumption after MB events and whether patients have continued on the same OAC before the MB event, switched to another OACs or received lone antiplatelet therapy.
7. To assess and compare patients' risk for stroke and bleeding recurrence using HAS-BLED, CHA2DS2-VASC, HEMORR?HAGES and GARFIELD-AF risk assessment scores, at the time of the indexed major bleeding event.

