According to previous studies, elderly patients (>85 years) are less likely to be prescribed anticoagulation therapy, this observation is well documented in several studies, and is mainly attributed to the overestimation of bleeding risk. Moreover, elderly patients with high risk for stroke and those with coronary artery disease are more likely to be prescribed only one antiplatelet therapy, despite the 2016 ESC guidance which state that antiplatelet monotherapy should not be used for stroke prevention in AF patients. Observational studies showed that under prescribing of OACs in high-risk AF patients is associated with higher rates of stroke rates and death. OACs prescribing is largely based on physician's assessment of benefit (reducing stroke risk) versus risk (potential for bleeding), while considering many patients related factors. An example to this, is patients with AF and cancer since their risks of venous thromboembolism (VTE) and of non-cardio embolic stroke are higher than in the general population and may have to factor into the decision for some cancer subtypes, and also the bleeding risk is often much higher in patients with cancer due to coagulopathies, thrombocytopenia, anaemia that increase the propensity towards bleeding events. This illustrates the risk–treatment paradox previously reported in AF management that patients at higher risk of stroke and who are more likely to benefit from OACs are not receiving appropriate treatment, due to their bleeding risk. A comparative evaluation of physicians' decisions to prescribe OACs or not in high risk AF patients and their associated clinical outcomes could yield more informative, actionable conclusions if it provides a focused evaluation of patients characteristics and co-morbidities to identify the type of high-risk AF patients who would benefit from OACs without experiencing bleeding events.

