**Covariates:**

- Patients' demographic information (age, gender, ethnicity, body mass index (BMI), geographic location (rural vs. urban), smoking status, alcohol consumption, Charlson comorbidity index for the severity of comorbidity (Appendix 4), electronic frailty index (eFI), and the index of multiple deprivation (IMD).
- For the sub-group of patients with NVAf and history of cancer, cancer diagnosis will be assessed at the index date of NVAf diagnosis and classified by cancer type into breast, prostate, colorectal, haematological, lung, and other types, and by cancer metastasis status.
- Drugs that affect either stroke or bleeding, or commonly interact with OACs, such as antihypertensive drugs, statins, antiarrhythmics, antidiabetic drugs, anticonvulsants, non-steroidal

anti-inflammatory drugs, corticosteroids, systemic azoles, HIV protease inhibitors and ciclosporin. (Appendix 2).

- The CHA2DS2-VASc stroke risk score that consists of 9 points, one for each of: congestive heart failure (CHF), hypertension (HTN), age  $\geq 75$  years (x 2 points), diabetes mellitus (DM), prior stroke or transient ischemic attack (TIA) or thromboembolism (x 2 points), vascular disease, age 65 to 74 years, and sex category. Information included in the CHA2DS2-VASc score will be identified using Read codes (Appendix 3 and 4), except for age and sex, to build the score and assess the risk of stroke for all included patients in the cohort. Further categorization of eligibility for OACs will be carried according to individual CHA2DS2-VASc scores; “not eligible for OAC” if CHA2DS2-VASc score = 0 in males, or 1 in females; and “OAC eligible” if CHA2DS2-VASc score  $\geq 1$  in males, or  $\geq 2$  in females.

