## **Data/statistical analysis**

1. Phase 1 - NVAF cohort: Annual and crude incidence rates of NVAF cases will be calculated and expressed as person-time at risk with 95% confidence intervals (95% CI). Incidence rates will be calculated by dividing the number of new diagnosed NVAF cases each year by the total population at risk during the same year. NVAF incidence in each calendar year of the study period (2009-2018) will be stratified by age and further standardized by age and deprivation quantiles. Status of anticoagulation therapy will be classified as either OAC prescribed or OAC not prescribed. OAC prescribed patients are those who received prescriptions for OACs during the study period. Treatment patterns for OAC users will be evaluated for OACs continuation, discontinuation or switched). OACs not prescribed will be defined as no prescription record of an OACs at any time after NVAF diagnosis, this will also include patients prescribed lone antiplatelet therapy. Proportions of patients prescribed antiplatelets will be described for both OACs prescribed and not prescribed patients. Baseline demographic, and clinical characteristics, and status of cancer diagnosis across OACs prescribed and not prescribed groups will be presented as number and percentage, mean $\pm$  (SD), or median (interquartile range), as appropriate. For both groups' eligibility for OACs will be described and categorized based on stroke risk according to CHA2DS2-VASc score. Trends in OACs initiation, switching from antiplatelet only to OACs, and from VKA to NOAC will be explored for each year and further stratified by eligibility for OACs and deprivation quantiles. To identify variables independently associated with OACs prescribing multivariate logistic regression models will be used and fitted with the covariates described in section N. Similarly, in a separate analysis for patients with NVAF and previously diagnosed cancer multivariate logistic regression models will be fitted to explore variables independently associated with OACs prescribing (i.e, cancer types and metastasis status). The level of statistical significance was set at  $P < 0.05$ .

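### Phase 1 cancer sub-group: with no term for time since cancer diagnosis, the cancer-type odds ratios may partly reflect how recent the cancer is (cheap improvement)

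*Protocol*

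**What the plan says.** Four parts of the protocol bear on this.

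- **Who is in the sub-group.** The Phase 1 covariate list introduces it with "For the sub-group of patients with NVAf and history of cancer". The Phase 1 paragraph of Data/statistical analysis repeats the idea: "in a separate analysis for patients with NVAF and previously diagnosed cancer multivariate logistic regression models will be fitted". Neither gives a look-back window.
- **How cancer is described.** The covariate list states that "cancer diagnosis will be assessed at the index date of NVAf diagnosis and classified by cancer type", with the types listed as breast, prostate, colorectal, haematological, lung and other, "and by cancer metastasis status". The analysis section gives the purpose of the model as "to explore variables independently associated with OACs prescribing (i.e, cancer types and metastasis status", the last words being a bracketed explanation of which variables are meant.
- **Whole-cohort use.** Aim 3, under Specific aims, lists among the factors to assess "socioeconomic status, history of cancer and other comorbidities, stroke and bleeding risk", again with no time limit. Aim 2 asks for the proportions prescribed OACs, antiplatelet alone or nothing in patients with NVAF and cancer.
- **Why cancer is studied.** The Study background argues that "bleeding risk is often much higher in patients with cancer due to coagulopathies, thrombocytopenia, anaemia", and also cites raised thromboembolic risk.

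No section gives an active-cancer definition, a remission rule, cancer treatment status or time since cancer diagnosis.

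**The concern.** Reading cancer status at the NVAF index date fixes when the record is examined. It does not require current disease, so a cancer coded decades earlier and one coded the month before enter the sub-group on equal terms. The mechanisms given in the Study background belong mainly to current disease or its treatment, so recency could plausibly influence whether an OAC is prescribed.

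Two separate results are affected.

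1. **Type odds ratios in the sub-group model.** Cancer types may differ in how many patients survive long enough to be diagnosed with NVAF years later. If so, they differ in their share of recent cancers, and a type odds ratio without a recency term mixes type with recency. The cancer-type comparison is one of the two outputs the protocol names for this model.
2. **Aim 2 proportion and Aim 3 term.** Each is an average over recent and remote cancers. If prescribing differs between the two, the average describes neither group well, and it depends on the mix in this cohort.

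**Working it through.** The protocol states no odds ratio, sample size or power for the cancer sub-group, so there is no figure of its own to reproduce. The calculation below only illustrates how large the effect could be.

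**Assumed inputs (none is in the protocol)**

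- Proportion not prescribed an OAC in remote cancer: p0 = 25%.
- Odds ratio for not being prescribed, recent versus remote cancer: 2.0, with a range of 1.5 to 3.0.
- Share of recent cancers, s: between 20% and 80%.
- No true effect of cancer type.

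**Formulas**

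- Odds in recent cancer = OR × p0/(1 − p0), converted to a risk p1.
- Risk in a group with recent share s: p(s) = s·p1 + (1 − s)·p0.
- Spurious type odds ratio = odds of p(s1) / odds of p(s2).

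**Risk in recent cancer**

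- OR 2.0: odds 2.0 × 0.25/0.75 = 0.667, so p1 = 40.0%.
- OR 1.5: odds 0.5, so p1 = 33.3%.
- OR 3.0: odds 1.0, so p1 = 50.0%.

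**(a) Type odds ratio in the sub-group model, crude**

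| Recent-cancer OR | 50% v 30% recent | Spurious OR | 80% v 20% recent | Spurious OR |
|---|---|---|---|---|
| 1.5 | 29.2% v 27.5% | 1.09 | 31.7% v 26.7% | 1.27 |
| 2.0 | 32.5% v 29.5% | 1.15 | 37.0% v 28.0% | 1.51 |
| 3.0 | 37.5% v 32.5% | 1.25 | 45.0% v 30.0% | 1.91 |

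For example, in the middle row, (0.325/0.675)/(0.295/0.705) = 0.4815/0.4184 = 1.15. With equal recent shares the ratio is exactly 1.

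A separate run took the outcome the other way round, as receiving an OAC with a recent-cancer odds ratio of 0.5. It gave 0.87 for 50% v 30% and 0.66 for 80% v 20%, the reciprocals of 1.15 and 1.51. To two decimals these did not change as the baseline proportion prescribed moved from 60% to 88%.

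**(b) Averaging in Aims 2 and 3**

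With OR 2.0, the pooled proportion not prescribed among patients with cancer is:

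- 20% recent: 0.2 × 40% + 0.8 × 25% = 28.0%
- 30% recent: 29.5%
- 50% recent: 32.5%

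These compare with 40% in recent cancer and 25% in remote cancer. To turn them into a history-of-cancer odds ratio against cancer-free patients, one must also assume that remote cancer carries the same odds as no cancer. Under that assumption the odds ratios are 0.389/0.333 = 1.17, 0.418/0.333 = 1.26 and 0.481/0.333 = 1.44, against 2.0 for recent cancer.

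**What the other covariates already capture**

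The Phase 1 covariates include the Charlson index and electronic frailty index. Through the HAS-BLED and HEMORR2HAGES scores they also include anaemia, low platelet count and malignancy, read at the index date. The cancer model follows directly on from the whole-cohort model and is introduced as similar to it, so these covariates probably enter it too. They act as partial markers of current disease. They cannot separate a recent from a remote non-metastatic cancer in patients without those abnormalities. The figures in (a) take no account of them and are therefore crude.

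**The case against.** The strongest case against is that this is a covariate preference in an exploratory analysis. The protocol calls Phase 1 hypothesis-generating, sets history of cancer as its target, and contradicts nothing in doing so. Describing prescribing by cancer type among patients with any cancer history is a legitimate answer to that aim. The bleeding scores, Charlson index and frailty index cover part of the mechanism. Code lists in the appendices, or a SAP that is not shown, could add a window. Every input to the illustration is assumed, and 80% versus 20% is an extreme contrast.

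Most of this stands. It limits the point to an improvement and rules out firm statements about size. Two things remain. First, the protocol does more than leave cancer classification open: it lists the two classifiers and names them again as the model's cancer variables, so a SAP that simply followed it would have no recency term. Second, the model is meant to find variables independently associated with prescribing, and for type that reading is weak when a plausible correlate, available from dated records, is left out.

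A reader might also infer that remote cancers dilute the cancer effect in the sub-group model. The protocol does not support that. The model contains only patients with cancer, so it has no cancer-free comparator and estimates no overall cancer effect. Averaging applies to Aims 2 and 3 only.

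**Conclusion.** The point holds as a cheap improvement. As written, the sub-group admits cancers of any age and models them by type and metastasis status. The type odds ratios **may** therefore be partly confounded by recency, on two conditions that the protocol neither states nor excludes: recency affects OAC prescribing, and the recent share differs between types. Metastasis status and the other covariates lessen the problem without removing it for non-metastatic cancers.

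The size cannot be derived from the protocol. With an assumed recent-cancer odds ratio of 2.0, the crude spurious type odds ratio is about 1.15 for a moderate contrast in recent shares and about 1.5 for an extreme one. The adjusted figure is probably smaller, by an unknown amount.

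It would go too far to say that the type comparison is confounded, or that the results will understate the withholding of OACs in current cancer. The first depends on the two conditions above. The second concerns a target, current cancer, that the protocol does not set. The odds ratios of 1.17 to 1.44 for any history of cancer depend further on treating remote cancer as equivalent to no cancer.

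**What to change.** In the Phase 1 covariate list, add time from the most recent cancer diagnosis to NVAF diagnosis, derived from the dated codes already needed to establish that a cancer came first. In the Phase 1 analysis paragraph:

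- enter this variable in the cancer sub-group model alongside type and metastasis status, either as recent versus remote with a cut-point fixed in advance or as a smooth term;
- report the Aim 2 prescribing proportions for recent and remote cancer separately;
- split the Aim 3 history-of-cancer term in the same way.

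The cost is one derived variable and slightly wider intervals within the recency strata. No new data source is needed. The protocol gives no size for the cancer sub-group, but its feasibility count of at least 120,000 incident NVAF cases in CPRD GOLD suggests that the loss of precision should be modest, except perhaps for the rarer cancer types.

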## Selection of comparison groups/controls

For the second phase of this study, we aim to compare the clinical outcomes of patients with NVAf prescribed OACs and who were not prescribed OACs. This will be done by including incident cases of NVAf identified from phase one cohort from 2009 to 2019 and further divide them into two groups; cases are patients treated with OACs within one year of NVAf diagnosis and controls are those who did not receive OACs for  $\geq 1$  year after NVAf diagnosis. Many confounders will be controlled for when evaluating the effect of treatment (OACs) on the clinical outcomes of interest (i.e. stroke, bleeding, or all-cause mortality). Potential confounders are likely to include patient age, sex, and presence of hypertension, diabetes, coronary artery disease, heart failure, kidney disease, liver disease, peripheral artery disease, fall risk, history of stroke or bleeding, malignancy, anaemia, alcohol abuse, antiplatelet use or non-steroidal anti-inflammatory drugs. At first, we aim to perform propensity score matching method using a multivariable logistic regression model that contains the confounders mentioned above to estimate patient's probability to receive OACs. Matching will operate by taking each case and finds the closest propensity score match among controls, within a predetermined caliper bandwidth. However, in case if the matching method failed to achieve balance among the two patient groups or caused substantial exclusion of individuals from the main cohort, then we will consider overlap propensity score weighting. By applying overlap propensity score weighting each patient's will be weight by the probability of that patient being assigned to the opposite treatment group.

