## 2. Phase 2 - Comparative study

**Exposures:** In this cohort, prescriptions for OAC will determine patient’s exposure status. NVAf patients identified from phase one and who have received a continuous prescription of either VKAs or NOACs within one year of NVAf diagnosis will be in the OACs “exposed group”. While “OACs unexposed” patients are individuals in phase one who haven’t received a prescription for anticoagulation therapy and remained OACs free for  $\geq 1$  year from NVAf diagnosis.

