2. Phase 2 – Comparative study: For comparison of demographic variables and comorbidities among OACs treated and not treated individuals, independent sample t tests will be used for numeric variables, while Chi squared  $\chi^2$  tests or Fisher exact tests will be used for categorical variables. To control for imbalances in patient characteristics between cohorts, we will calculate an exposure-specific propensity score as the predicted probability of receiving OACs conditional upon individuals baseline covariate (as described in section M) using logistic regression models. Then we will consider applying propensity score matching methods to match each OACs unexposed controls to up to 5 NVAF OACs exposed cases using a calliper of 0.2 standard deviation (SD) of the propensity score logit. After matching, Cox regression will be used to compute hazard ratios (HRs) of the outcomes of interest, comparing exposure to OACs versus no OACs. Initially crude HRs will be obtained, then stratified by type of OACs (i.e., VKAs and NOACs) and adjusted for age, and other important covariates described in section N. In this phase immortal time bias would occur due to the definition of exposure, where in the time from AF diagnosis till receipt of OACs those in the “OACs prescribed group” cannot have the outcome by design, otherwise they would have been classified as non OAC users. To avoid the problem of immortal time bias, we will consider using time-varying exposures, where in a survival analysis, the time period previous to the index date of OACs initiation is reclassified as nonuser for those in the “OACs prescribed group”.

3. Phase 3 – Major bleeding events cohort: At first, we will use descriptive statistics to present the overall characteristics of this cohort who have experienced major bleeding events while taking OACs. After that patients will be divided to 2 groups one for the patients who resumed anticoagulation after the index major bleeding event and the other for the group who remained OACs free and will compare the patient characteristics between the two groups using Chi squared  $\chi^2$  tests, Fisher's exact tests, and analysis of variance, as appropriate. Survival (time-to-event) models will be constructed to compare the time between the indexed major bleeding to the earliest event of stroke, bleeding, or all-cause mortality considering if patients were restarted on OACs or not. In Cox models we will control for age, time to OACs resumption, CHA2DS2-VASc

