### **Plan for addressing confounding**

In phase 2, we aim to conduct a comparison between NVAF patients who were exposed to OACs (cases) and patients who were not exposed to OACs (controls). We will calculate an exposure-specific propensity score as the predicted probability of receiving OACs conditional upon the effect of potential confounders (described in section M). Then we will use a propensity score matching method to achieve similarity of measured confounders across cases and control groups. When estimating HRs using Cox regression models for the outcomes of interest among patient groups, we will also adjust for age, sex, IMD, stroke risk, bleeding risk, frailty, Charlson comorbidity index, and prescription of antiplatelets.

In phase 3, when looking at the predictors of restarting OACs after the indexed bleeding events we will take in account many confounders that could influence this decision, this will be done by using a multinomial logistic regression to adjust for the covariates described in section N. These covariates will also be considered when conducting survival analysis to compare the time between the indexed major bleeding to the earliest event of stroke, bleeding, or death among patients who restarted OACs and those who did not. Also, when evaluating the outcomes of restarting OACs we will consider the timing of restarting anticoagulation after bleeding, and stratify patients based on different time periods of OACs reinitiating.

In both phase 2 and 3, an additional analysis will be considered to assess the robustness of results to unmeasured confounding using the E-value methodology. This estimates what the relative risk would have to be for any unmeasured confounder to overcome the observed association of OACs prescribing with the clinical outcomes of stroke, bleeding, or mortality.

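### Phase 2 reports VKA and NOAC hazard ratios after matching on a single any-OAC propensity score, which does not guarantee balance against controls for either drug group

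*Protocol*

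**What the plan says.** **Score.** The protocol's Data/statistical analysis section, Phase 2, states: "we will calculate an exposure-specific propensity score as the predicted probability of receiving OACs conditional upon individuals baseline covariate". Plan for addressing confounding repeats the definition, and Selection of comparison groups/controls describes a "multivariable logistic regression model that contains the confounders mentioned above to estimate patient's probability to receive OACs". All three model the same two-way exposure, any OAC against none.

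**Exposed group.** Under Exposures, outcomes and covariates, Phase 2, the exposed are those "who have received a continuous prescription of either VKAs or NOACs within one year of NVAf diagnosis". VKA and NOAC users form one group.

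**Matching.** Each unexposed patient is matched to up to five exposed patients within a calliper of 0.2 SD of the logit of the score, with no condition on drug type. If matching fails, overlap weighting is considered, again for the OAC versus no-OAC contrast.

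**Results by drug.** After matching, crude HRs come first; they are "then stratified by type of OACs (i.e., VKAs and NOACs) and adjusted for age, and other important covariates described in section N". Plan for addressing confounding gives the adjustment set: "we will also adjust for age, sex, IMD, stroke risk, bleeding risk, frailty, Charlson comorbidity index, and prescription of antiplatelets".

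The protocol describes no drug-specific score, no re-matching or re-weighting by drug, and no balance check by drug.

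**The concern.** A propensity score balances the groups whose membership it models. Here those groups are OAC and no OAC. Splitting the matched OAC patients by drug creates two groups that the score did not model. If the choice between a VKA and a NOAC depends on prognostic covariates, each drug group can differ from the controls even though the two together do not. A pooled balance table would look satisfactory and would not reveal it.

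At stake are the type-specific HRs. A reader would naturally take them as coming from a balanced cohort, whereas protection against confounding in those two contrasts would rest largely on the covariate adjustment in the Cox model.

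**Working it through.** The plan gives no figure for balance or for the type-specific HRs, so there is none to reproduce. The Phase 2 sample size does not bear on this point.

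**1. Which exposure is modelled.** The word exposure-specific might suggest one score per drug. The same phrase defines it otherwise: "exposure-specific propensity score as the predicted probability of receiving OACs". Controls have no OAC type, so stratifying by type most naturally means two HRs, VKA v none and NOAC v none.

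**2. Why imbalance can hide.** Let d_V and d_N be the differences in a covariate mean between VKA users and controls and between NOAC users and controls, and let w_V and w_N be the shares of the two drugs among matched OAC patients. Pooled balance requires

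w_V × d_V + w_N × d_N = 0.

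This holds when both differences are zero, but also when they are non-zero with opposite signs.

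**3. Size before adjustment.** Assumed inputs, none from the protocol: factor prevalence 20% in controls, 12% in NOAC users and 28% in VKA users; equal numbers on each drug, so the pooled prevalence is (12% + 28%)/2 = 20%; the factor multiplies the hazard equally in all groups.

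Multiplier on the HR = [1 + p_type × (HR_f − 1)] / [1 + 0.20 × (HR_f − 1)]

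| Factor HR (HR_f) | NOAC | VKA |
|---|---|---|
| 2 | 1.12/1.20 = 0.93 | 1.28/1.20 = 1.07 |
| 3 | 1.24/1.40 = 0.89 | 1.56/1.40 = 1.11 |

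The bias is about 7% to 11% per drug. The VKA-to-NOAC ratio is multiplied by 1.28/1.12 = 1.14 to 1.56/1.24 = 1.26.

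**4. Direction.** Apply the multipliers for a factor HR of 2 to assumed true HRs.
- VKA 0.60, NOAC 0.80: these become 0.60 × 1.067 = 0.64 and 0.80 × 0.933 = 0.75. The ratio moves from 0.75 to 0.86, so the drugs look more alike.
- VKA 0.80, NOAC 0.60: these become 0.85 and 0.56. The ratio moves from 1.33 to 1.52, so the drugs look less alike.

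**5. Simulated matching (illustrative).** The assumptions were one standardised confounder, about 86% treated, a 0.2 SD calliper on the logit, and up to three treated patients per control (the plan allows five). Standardised differences are against all matched controls:

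| Log-odds of NOAC v VKA per SD of confounder | Pooled OAC | VKA | NOAC |
|---|---|---|---|
| 0 | 0.00 | 0.00 | 0.00 |
| 0.2 | 0.00 | −0.10 | +0.10 |
| 0.4 | 0.00 | −0.18 | +0.16 |
| 0.8 | 0.00 | −0.36 | +0.29 |

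With a single confounder, patients with equal scores have equal covariates, so comparing each VKA user only with its own matched control would remove the difference in this example. With several confounders that no longer follows, because patients with the same score can have different covariate patterns and the drug choice may depend on them.

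**6. What the Cox adjustment covers.** The propensity list includes kidney disease, liver disease and fall risk as separate variables. The Phase 2 covariates bring these in through scores: HAS-BLED counts kidney and liver function, HEMORR2HAGES counts hepatic or renal disease and falls, and GARFIELD-AF includes chronic kidney disease. They are therefore represented, although in the two bleeding scores as fixed points in a sum that need not match each factor's effect on stroke or death.

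**The case against.** The strongest reply is that the sentence announcing the type-specific HRs also says they are covariate-adjusted, and that the adjustment set is broad. The multipliers above apply to unadjusted HRs, and nothing in the document allows the bias left after adjustment to be computed. That stands. The result is also subsidiary: the aim for this phase is OAC against no OAC, and no Phase 2 aim compares VKA with NOAC. For stroke, the sample-size section's planning rates give a ratio of 2.8/8 = 0.35; a 7% bias moves it to between 0.33 and 0.37, which would not change the conclusion. An analysis plan that is not shown might add drug-specific scores, although the protocol itself fixes one.

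Several stronger readings are tempting and are not supported:
- *That both drug groups will be unbalanced.* If drug choice is unrelated to the confounders, balance holds, as the first row of the simulation shows.
- *That the drugs will look more different than they are.* Step 4 shows that the gap can widen or narrow.
- *That kidney disease, liver disease and falls go unadjusted.* They enter through the risk scores.
- *That the protocol claims matching balances each drug group.* It claims similarity only between OAC-exposed and unexposed patients.

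None of this answers the central point: one any-OAC score does not secure balance for two contrasts that it does not model.

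**Conclusion.** The point holds as a limited weakness in the type-specific HRs. Balance against controls is not assured for VKA users or for NOAC users, under either matching or the overlap-weighting fallback, and a pooled balance check would not show a failure. The planned adjustment reduces the resulting confounding but does not restore balance on the individual propensity variables. What remains is of unknown size and direction.

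The 7% to 11% per drug is an order of magnitude before adjustment. It rests on assumed prevalences of 12% and 28%, an equal split between drugs and a factor HR of 2 to 3. It is not an estimate of bias in the planned, adjusted HRs.

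A reader might infer that the main Phase 2 result is compromised. It is not: the score matches the any-OAC contrast, and that HR is not affected by this point.

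**What to change.** For the type-specific HRs, estimate separate propensity scores (VKA v no OAC and NOAC v no OAC) or one multinomial score. Match or overlap-weight within each contrast, and report a balance table for each. Keep the any-OAC score for the overall contrast only, and say in Data/statistical analysis which score supports which HR.

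The cost is two further models on the same data and somewhat smaller matched sets per drug. The feasibility section expects around 14,000 patients not treated with OACs, so size should not be an obstacle.
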